## Abstract

**Background:**

Child marriage hinders progress toward population health and development goals. Cost effective interventions that address the root causes of child marriage are needed to speed progress toward ending the practice. Nigeria is home to the largest number of married girls in Africa and many of these girls are members of the Hausa ethnic group, making efforts to tackle this issue particularly urgent among this population.

**Methods:**

Radio programs have the potential to inform large numbers of people about the harms of child marriage and change their support for the practice at low cost. We will develop a series of radio programs that address gender inequitable attitudes that motivate child marriage among Hausa communities in Ibadan, Nigeria. The content of the series will be based on input from the Hausa community. A baseline survey that measures knowledge of and support for child marriage will be conducted among randomly selected samples of Hausa adults in two cities: Ibadan, which will serve as the intervention site, and Akure, the control site. The radio programs will then air on Hausa-language stations in Ibadan over a three-month period, with the aim of informing persons of the potential harms of child marriage and reducing their support for the practice. A follow-up survey with the same individuals surveyed at baseline will be conducted in both cities. We will measure the impact of this intervention by comparing changes in these outcomes over time in the intervention site (Ibadan) with changes in the same outcomes in the control site (Akure).

**Conclusion:**

This study will investigate whether a series of targeted radio programs can reduce support for child marriage. The intervention is readily scalable and cost-effective and, if it effectively shifts attitudes toward child marriage, could represent a promising way of addressing child marriage in Nigeria.

## Introduction and rationale

Child marriage, defined as marriage before 18 years of age, is a violation of human rights with harmful consequences for population health and development [1, 2]. Girls are far more likely to marry as children than boys, and so the consequences of child marriage exacerbate existing gender inequities across much of the globe. Child marriage cuts short girls’ education [3, 4], increases their likelihood of living in poverty in adulthood [5], and is strongly and consistently correlated with early childbearing, lack of access to maternal health care, and intimate partner violence [2]. The prominence of child marriage on global health and development agendas is reflected by the fact that the United Nations Sustainable Development Goals call for elimination of the practice by the year 2030 [1].

Child marriage is ongoing throughout most of the world despite intensifying efforts to eliminate it [6]. At its core, the practice is driven by the belief that girls are less valuable than boys. Often, these beliefs intersect with poverty to result in child marriage. To illustrate, if a family of limited means can only afford to educate some of their children, they may see more value in sending their male children to school. In the absence of educational or economic opportunities, female children may then be married at young ages. Child marriage frequently reflects efforts to control girls’ sexuality as well. Girls may be married at young ages to prevent them from engaging in consensual premarital sex or in an effort to prevent sexual violence where unmarried women are more likely to be targeted [7, 8].

Many interventions intended to curb child marriage have been fielded in recent decades. Since 2011, three systematic reviews have attempted to identify interventions that are most effective at meeting that aim [9–11]. The most recent review by Malhotra and Elnakib included 34 randomized or quasi-experimental studies published between 2000 and 2019 [9]. The authors concluded that interventions that increased young girls’ access to schooling and those that provided cash or other in-kind assets to their families showed the most consistently positive results for slowing child marriage rates. The interventions, which primarily included large scale (e.g., national) conditional cash transfer programs or efforts to improve educational and economic opportunities for girls, seem to hold great promise. However, they are also very expensive for governments to fund and sustain, particularly those in resource-limited settings with the highest rates of child marriage. Moreover, these interventions do not directly address the gender inequitable beliefs that are a root cause of child marriage. Interventions that provide cash or other material goods that facilitate girls’ access to schooling can prevent scenarios like those described above, but they do not necessarily change the underlying gender norms that devalue girls. Recent research shows that gender norms are malleable [12, 13]. For example, an educational intervention among adolescents in India found that classroom discussions about gender equality led to a sustained reduction in support for social norms that devalued women and girls [13].

In order to make meaningful progress toward eliminating child marriage by the year 2030, interventions must be both effective and highly scalable–politically, logistically, and financially– and on a relatively short timeline. Financial scalability is particularly important at this moment in history because child marriage interventions may compete for public resources being devoted to addressing the ongoing COVID-19 pandemic and its long-term impacts in many domains. Targeted media messaging may be a cost-effective means of changing gender norms. This study will evaluate whether radio programming designed to address highly localized motivations for child marriage can modify attitudes toward the practice in Ibadan, Nigeria.

### Child marriage in Nigeria

Nigeria is home to the largest number of married girls in Africa [14]. National rates of child marriage have remained stubbornly high in recent decades despite domestic and international efforts to address the issue [15, 16]. According to the 2018 Demographic and Health Survey, 43% of Nigerian women between 20 and 24 years of age married before their 18^th^ birthdays [17]. However, the frequency of child marriage varies widely across the country and is much higher in the northern and north eastern regions, where the prevalence is greater than 70% in some states [17]. These geographic differences in child marriage are correlated with state-level laws regarding the practice, ethnicity, and violent conflict.

Twenty-eight of 36 Nigerian states have adopted the federal *Child Rights Act*, which makes marriage before the age of 18 illegal [18, 19]. All states that have thus far refused to adopt the *Act* are located in the north [19], meaning that child marriage is not legally prohibited where it is most commonly practiced. Government representatives in these states have used religious and cultural arguments to justify their opposition to the *Act* [20, 21]. Child marriage rates also vary markedly across ethnic groups in Nigeria. A recent study based on a nationally representative sample found that 55% of Hausa girls between the ages of 15 and 19 were married, a prevalence more than ten times as high as that among the other two major ethnic groups in the country (Yoruba (3%) and Igbo (4%)) and twice as high as among minority ethnic groups in Northern Nigeria [22]. These ethnic differences are strongly correlated with the geographic variation already discussed: the northern states of Nigeria account for the largest concentration of persons of Hausa ethnicity living in the country. In addition, many of these states have been affected by violent conflict for several decades, resulting in substantial migration of Hausa persons from northern to southern regions of the country [23]. Both conflict and migration are likely to exacerbate the drivers of child marriage. Where conflict involves an increased risk of sexual violence, marriage may be seen as a means of protection against sexual assault, thereby increasing the incentive for girls to marry at very young ages. Migration may lead to economic hardship and families may arrange the marriage of young girls to lessen the financial burden of caring for them [24]. In the scenarios described above, it is likely that decisions regarding the marriage of young girls are made by adult members of their families and not by the girls themselves, or at least not exclusively [25]. For these reasons, our intervention will target Hausa adults.

## Methods

### Study setting

The study will be conducted in two cities in southwest Nigeria: Ibadan and Akure. Ibadan will serve as the intervention site and Akure as the control site. Ibadan was selected as the intervention site because one of the principal investigators of this project ([name]) is a community physician with strong professional networks throughout the city and institutional support from the College of Medicine at the University of Ibadan. Akure was selected as the control site because it is located in a neighbouring state with similar social, demographic, and geographic characteristics but is outside the broadcast range of radio stations in Ibadan, which will limit spill over of the intervention and, pragmatically, reduce the logistic burden of collecting data in both sites during a short-term project. Both Ibadan and Akure are located in states that legally prohibit marriage before the age of 18. In addition, both cities receive a substantial number of Hausa immigrants from the northern states of the country.

### Intervention

We will develop a series of radio dramas intended to reach members of the Hausa community aged 40 years and older who reside in Ibadan, Nigeria. Radio is an appropriate means of reaching this population. Many Hausa persons living in Ibadan migrated to Southwest Nigeria from northern regions of the country and reside in informal housing settlements in the city. Television is beyond the financial means of many households, and radio is often listened to as a collective social activity among adults. Recent research demonstrates that radio is an important source of public health information in the country [26].

The programs will include fictional storylines that address gender norms that motivate child marriage and will highlight the harms of the practice. The content of the radio dramas will be informed by qualitative research that is currently underway. Our research team is conducting focus group discussions and key informant interviews with Hausa community members living in Ibadan to understand how child marriage is perceived, its potential benefits and harms, and why it is ongoing. The results of this qualitative research will provide the basis for storylines in the radio dramas that counter gender inequality and address the specific motivations for child marriage within the community. The radio dramas will be professionally scripted and produced by the Shield of Innocence Initiative, a non-governmental organization that specializes in developing social messaging for media outlets, with assistance from the Biomedical Communication Centre of the University of Ibadan College of Medicine [27, 28]. A Local Advisory Committee composed of ten Hausa community leaders from Ibadan, including religious authorities, will review the radio dramas prior to broadcasting to ensure that the content is culturally appropriate and compelling.

We have budgeted to air the radio dramas three times per week on three separate Hausa-language stations based in Ibadan over a three-month period in 2023. Incentives will be provided to promote listenership. At the end of each radio drama, listeners who correctly respond to a question about the content will be entered into a drawing for pre-paid mobile phone credit. Two local Hausa celebrities will also be hired to participate in the dramas to increase their appeal to a broad audience. We verified that the broadcast range of these stations does not extend to Akure, the control city, but some of these stations allow listeners to tune into their programming online. This means that some degree of spill over of the intervention is possible. However, our target population includes persons aged 40 and older, whom we believe are unlikely to seek out online radio broadcasts, and we will look for evidence of spill over in Akure during the follow-up survey.

### Research objectives

We aim to learn whether the targeted radio intervention described above improves knowledge about child marriage and influences support for the practice among adult members of the Hausa community residing in Ibadan, Nigeria. Our specific objectives are:

To determine whether targeted radio broadcasts can effectively reach Hausa communities in IbadanTo determine whether the targeted radio broadcasts improve knowledge of the harms of child marriageTo determine whether the targeted radio broadcasts change support for child marriage among members of the Hausa community in Ibadan

### Research design

We will measure the impact of our intervention using a controlled, pre-post design. A baseline survey will be conducted in both cities prior to the intervention to measure knowledge and perceptions of child marriage, including the ideal age for marriage among boys and girls, the perceived benefits and harms of marrying early, and knowledge of the minimum age for marriage specified by law. The baseline questionnaire was written in English and will be translated into Hausa and Yoruba, the primary languages spoken among Hausa persons living in Ibadan and Akure.

The radio dramas will be broadcast in Ibadan for a period of three months. Afterward, we will follow up with the same individuals who participated in the baseline survey in both cities and ask them to complete a second interview. The follow-up interview will measure coverage of the intervention, i.e., whether participants heard the radio dramas, and will ask many of the same questions as the baseline interview so that we can measure changes in these outcomes over time.

### Pre-determined outcomes and sample size calculations

During the process of applying for funding for this research, the authors were required to specify a threshold for demonstrating “proof-of-concept” to the funding agency, Grand Challenges Canada (GCC) [29]. (Under GCC’s funding model, projects that demonstrate proof-of-concept may be eligible for expansion and longer-term funding). The authors and the funding agency agreed in advance on the outcomes and the minimum relative change in those outcomes that would be considered sufficient evidence to demonstrate that the intervention seems promising, i.e., demonstrates proof-of-concept:

A 10% increase in the proportion of participants who can identify at least one harmful consequence of child marriage for girls’ health, education, and/or economic opportunitiesA 20% increase in the proportion of participants who know that marriage before the age of 18 is illegal in Oyo State, Nigeria (where Ibadan is located)A 10% reduction in the proportion of participants who believe that the ideal age for girls to marry is younger than 18A 10% reduction in the proportion of participants who would support the marriage of girls in their families before the age of 18.

These pre-determined outcomes and the specified minimum change in those outcomes guided our sample size calculations. We want to be sure that we have sufficient statistical power to detect the effect sizes described above with a high degree of precision and, ideally, to detect even smaller effects. Assuming that 20% of persons surveyed at baseline already have the outcome of interest, we estimate that with a sample of 1600 persons, 50% of whom will be assigned to the treatment group (i.e., living in Ibadan), we can detect a minimum change of five percentage points in each outcome with 80% power at an alpha level of 0.05 [30].

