### Sampling procedure

Participants will be recruited through a multi-stage cluster sampling approach. In the first stage, enumeration areas (called settlements) within known Hausa neighbourhoods (wards) of Ibadan and Akure will be randomly selected from existing lists developed by health care centres in those wards. In the second stage, houses within selected enumeration areas will be randomly selected using lists obtained from the Nigerian National Population Commission (NPC). Multiple households often reside within the same residential building in these cities. Every household in a selected building that includes at least one eligible participant will be invited to participate. If households include more than one eligible participant, one individual will be randomly selected. If buildings selected from the NPC lists are abandoned or not in residential use at the time of the survey, new buildings will be randomly selected to replace them. Using this sampling approach, we will randomly select a total of 1600 persons to participate: 800 in Ibadan and 800 in Akure.

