### Variables to be measured

The baseline survey will record demographic characteristics of participants to determine how exchangeable intervention and control samples are prior to the intervention. The baseline and follow-up surveys will also collect information on participants’ knowledge and perceptions of child marriage. These questions will be worded identically on both surveys to facilitate measurement of change following the intervention. The baseline survey questionnaire is included in the appendix. We have several outcomes of interest. Those necessary for demonstrating proof-of-concept to the funding agency are:

The proportion of persons in Ibadan who report having listened to at least one radio drama during the intervention period. This will be assessed using the question, “Did you hear stories about child marriage broadcast on [radio stations] in the past few months?”The proportion of persons who are aware that marrying before the age of 18 is illegal in Oyo and Ondo state, where Ibadan and Akure are respectively located. This will be measured by correct responses to the question, “According to the law, what is the youngest age at which a person can get married in [Oyo or Ondo] State?”The proportion of persons who believe that the ideal age for girls to marry is younger than 18 years. This will be measured by responses to the question, “In your opinion, what is the ideal age for a girl to get married?”The proportion of persons who would support the marriage of girls in their families before the age of 18, measured based on responses to the question, “Would you support the marriage of a girl in your family before she turned 18?”The proportion of persons who correctly identify at least one harmful consequence of child marriage, as indicated through pre-defined responses to the question, “What are the possible harms to a girl if she marries before she turns 18?”

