### Statistical analyses

We will measure the impact of our intervention by comparing the change in outcomes between baseline and follow up in the intervention site (Ibadan) with the change in outcomes between baseline and follow up in the control site (Akure). Outcomes will be modelled using the following basic equation:

$$Y_{i}=\alpha +\beta C_{i}+{\gamma T}_{i}+\delta (C_{i}*T_{i})$$

This model posits that the outcome for an individual *i* (*Y_i_*) is a function of the city they live in (*C_i_*) and the time point *T_i_* (baseline or follow-up). The coefficient *δ* represents the treatment effect we are interested in. We will use the coefficients obtained from a logistic regression model to estimate the marginal probability of each outcome among the intervention and control samples and subtract these estimates to calculate risk differences.

Demographic covariates measured at baseline may be added to this model to account for any observed differences between intervention and control samples at baseline.

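### The proof-of-concept thresholds are relative changes with no stated comparator or precision criterion, and nothing ties them to the planned Ibadan-versus-Akure contrast

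*Protocol article*

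**What the plan says.** In *Pre-determined outcomes and sample size calculations*, the authors and the funder fix "the minimum relative change in those outcomes that would be considered sufficient evidence to demonstrate that the intervention seems promising". Four thresholds follow. The first is "A 10% increase in the proportion of participants who can identify at least one harmful consequence of child marriage"; the others are a 20% rise in knowledge of the legal age and 10% falls in two measures of support. The section then treats these as effect sizes that the study should have power to detect. Its power statement begins "Assuming that 20% of persons surveyed at baseline already have the outcome of interest" and concludes, "with a sample of 1600 persons, 50% of whom will be assigned to the treatment group", that "we can detect a minimum change of five percentage points in each outcome with 80% power at an alpha level of 0.05". *Sampling procedure* gives the split as "800 in Ibadan and 800 in Akure".

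*Statistical analyses* measures impact by "comparing the change in outcomes between baseline and follow up in the intervention site (Ibadan) with the change in outcomes" in Akure. The effect is the city-by-time interaction of a logistic model, converted to risk differences through marginal probabilities.

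*Variables to be measured* introduces its list with "Those necessary for demonstrating proof-of-concept to the funding agency are" and names five outcomes. The first, reach of the broadcasts in Ibadan, has no threshold in the earlier section.

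**The concern.** The threshold section states a decision rule, and meeting it may open the way to expansion and longer-term funding. The rule leaves three things open that determine what it means: whether the change is net of Akure, how a relative change relates to the planned risk differences, and how precise the estimate must be. It also does not say whether one or all outcomes must be met.

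The same people answer identically worded questions twice, so some gain in knowledge or shift in stated attitude could come from retesting or from a trend common to both cities. The control city is there to remove exactly that. If the rule is applied without it, or to a point estimate alone, an ineffective intervention can be declared promising.

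**Working it through.** **Inputs from the protocol article.** Baseline 20%; 800 people per city; detectable change 5 points; power 80%; alpha 0.05 (sidedness not stated); thresholds 10% and 20% relative. **Assumptions.** Within-person correlation rho, design effect, drift, no dropout, and any baseline other than 20%.

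**1. The plan's own figure.** Five points can be reproduced in two ways:
- One-sided alpha, simple two-group comparison: (1.645 + 0.842) × sqrt(0.16/(0.25 × 1600)) = 2.487 × 2.00 = 4.97 points.
- Two-sided alpha, difference in changes with rho = 0.6: SE = sqrt(4 × 0.4 × 0.16/800) = 1.789 points, and 2.802 × 1.789 = 5.01 points.

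A two-sided two-proportion comparison does not reach it: power is 66.8% for 20% to 25% and 75.0% for 20% to 15%. Taking the claim as two-sided, the implied SE is 5/(1.96 + 0.842) = 1.785 points; if one-sided, 5/2.487 = 2.01 points.

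**2. Thresholds in points at the plan's baseline.** 10% × 20% = 2 points; 20% × 20% = 4 points. Both are below 5.

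**3. Reading A: the change in Ibadan alone, no intervention effect.** SE = sqrt(2 × 0.16 × (1 − rho)/800), which is 1.67 points at rho 0.3 and 1.26 at rho 0.6. The chance of meeting a 10% item is P(Z > (2 − drift)/SE):

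| Drift or retest gain | rho 0.3 to 0.6 |
|---|---|
| 2 points | 0.50 |
| 3 points | 0.72 to 0.79 |

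The 0.50 follows directly from setting the drift equal to the threshold. Its message is how small that drift is. With no drift at all, over rho 0 to 0.7 and design effect 1 to 2, the chance is 0.03 to 0.24.

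**4. Reading B: the controlled point estimate, no effect.**
- 10% item: P(Z > 2/1.785) = 0.131.
- 20% item: P(Z > 4/1.785) = 0.0125.
- 10% item with design effect 1.5 or 2: 0.18 or 0.21.
- 10% item with the one-sided SE of 2.01: 0.16.
- 10% item over rho 0 to 0.7 and design effect 1 to 2, with the SE built from the sample size: 0.10 to 0.31.

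**5. Dependence on baseline.** At an assumed 50% baseline the 10% threshold is 5 points and the SE scales by sqrt(0.25/0.16) = 1.25 to 2.23. Reading B then gives P(Z > 5/2.23) = 0.0125. Reading A gives 0.03 to 0.08 for a 2-point drift and 0.10 to 0.17 for a 3-point drift.

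**6. Power if the interval must exclude no effect.** With SE 1.785 and a two-sided 5% test:
- 2 points: P(Z > 1.96 − 1.12) = 0.20.
- 4 points: P(Z > 1.96 − 2.24) = 0.61.

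Over the wider assumptions in step 4, power is 7% to 25% at 2 points and 17% to 73% at 4.

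**7. The two lists.** *Variables to be measured* has five outcomes; the threshold section has four. The extra one is reach, which is asked only at follow-up and so cannot have a relative change from baseline.

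**The case against.** The strongest reply is that the thresholds were always meant for the controlled contrast. The same section calls them effect sizes and sizes a two-group comparison for them, *Research design* describes a controlled pre-post study, and the analysis takes the interaction as the effect. A relative change can be computed from the marginal probabilities already planned. The funder's full criteria are not shown, and meeting the thresholds only makes a project possibly eligible for more support.

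Much of this stands. Because the legal-age threshold names Oyo State alone, a reader might infer that Akure plays no part and that the rule is a raw Ibadan change. The article does not say so: it is silent on the comparator, and *Variables to be measured* restates that outcome for both Oyo and Ondo. A reader might also combine the four items into a chance of passing at least one, 1 − (0.869³ × 0.9875) = 0.35. That assumes independent items and that one pass is enough, and the article states neither. If all four were required, the same inputs give 0.131³ × 0.0125, about 0.00003, though drift shared across items would remain.

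What the reply does not supply is the link itself. No section says that the thresholds are read on the interaction contrast, and even on that reading a point estimate alone counts as sufficient evidence.

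**Conclusion.** The point holds as a defect in how the decision rule is fixed. The rule is not tied to the planned contrast, its relative scale is not mapped to risk differences, and it has no precision criterion. At the 20% baseline, an ineffective intervention meets a 10% item about half the time under a 2-point drift if Ibadan is judged alone, and about 13% of the time by chance if the controlled point estimate is used. The 13% rests on an SE of 1.785 points inferred from the power statement taken as two-sided. It rises with clustering and falls to about 1% at an assumed 50% baseline.

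The list mismatch (five against four) is a plain inconsistency. So is the claim of sufficient power for the thresholds: at the plan's own baseline they are 2 and 4 points, below its 5-point detectable change. The planned impact estimate itself remains usable.

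**What to change.** - State that each threshold is judged on the Ibadan-minus-Akure difference in changes from the *Statistical analyses* model, divided by the model-based Ibadan proportion expected at follow-up without the intervention. Say whether that counterfactual is formed on the logit or the probability scale, and use it in both numerator and denominator.
- Report each estimate with a 95% interval that allows for clustering and repeated measures. Claim proof-of-concept as evidence of effect only where the threshold is reached and the interval excludes no effect.
- Use one list of outcomes in both sections. Give reach an absolute threshold or remove it from the necessary outcomes.
- State whether all outcomes must be met.
- Acknowledge that at a 20% baseline the thresholds lie below the 5-point detectable change.

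The cost is wording to be agreed with the funder, with no new data collection. Success becomes materially harder to claim: power is about 20% for a true 2-point effect and 61% for 4 points. Subtracting Akure removes only drift that the two cities share; an event particular to one city would still be counted as effect.

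### The stated 80% power for a five-point change does not reproduce two-sided, leaves no room for clustering or loss, and sits above the proof-of-concept thresholds it is meant to serve

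*Protocol article*

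**What the plan says.** All from the protocol article.

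- **Pre-determined outcomes and sample size calculations.** The power statement begins "Assuming that 20% of persons surveyed at baseline already have the outcome of interest, we estimate that with a sample of 1600 persons", with "50% of whom will be assigned to the treatment group" (that is, living in Ibadan). It claims 80% power at alpha 0.05 for a minimum change of five percentage points in each outcome. Sidedness, formula, within-person correlation, design effect and allowance for loss are not given.
- **Same section.** Four thresholds were agreed with the funder and are described as relative changes: a 10% increase in naming a harm, a 20% increase in knowing the law, and 10% reductions in each of two attitude outcomes. The authors want enough power for these effects and, ideally, for smaller ones.
- **Sampling procedure.** "Participants will be recruited through a multi-stage cluster sampling approach": settlements, then buildings, then every eligible household in a selected building. "Using this sampling approach, we will randomly select a total of 1600 persons to participate: 800 in Ibadan and 800 in Akure".
- **Data collection and management.** A relative or friend may be contacted to keep losses down, so some loss is anticipated.
- **Statistical analyses.** The effect of interest is the city-by-time interaction, a difference in changes between the two cities.
- **Limitations.** The study is described as powered for relatively small effects.

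**The concern.** The power statement gives baseline, total, allocation, effect, alpha and power, so it can be checked. It appears too favourable for a plain comparison of two proportions. The planned estimate also subtracts two changes, which adds variance unless the two answers from one person are well correlated. The number recruited equals the number in the calculation, so nothing is held back for clustering or for people who are not re-interviewed. Finally, a relative threshold applied to a 20% baseline is a small absolute change.

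At stake is how a null or small result will be read. The study feeds a proof-of-concept decision on further funding. A reader who trusts the stated power could take a non-significant result as evidence that the dramas do not work, when the study had limited ability to show it.

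**Working it through.** **Inputs from the protocol article.** Baseline 0.20; 800 per city; change 0.05; alpha 0.05; power 80%. Two-sided is taken as the convention, since sidedness is not stated. Correlation, design effect and loss below are assumptions, because the article gives none.

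**1. The plan's own figure, simple comparison of two proportions.**

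n per city = [1.960 × √(2p̄(1−p̄)) + 0.842 × √(p1(1−p1) + p2(1−p2))]² / d²

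- 20% to 25%: p̄ = 0.225. [1.960 × √0.34875 + 0.842 × √0.3475]² / 0.0025 = (1.1575 + 0.4961)² / 0.0025 = 1,094.
- 20% to 15%: p̄ = 0.175. [1.960 × √0.28875 + 0.842 × √0.2875]² / 0.0025 = (1.0532 + 0.4513)² / 0.0025 = 906.

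Power at 800 = Φ[(0.05 × √800 − first term) / √(p1(1−p1) + p2(1−p2))]

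- Increase: (1.4142 − 1.1575) / 0.5895 = 0.436, power 66.8%.
- Decrease: (1.4142 − 1.0532) / 0.5362 = 0.673, power 75.0%.

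Unpooled and arcsine versions also give 67% and 75%. The change detectable with 80% power is 5.9 points upward or 5.3 points downward.

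**2. Other readings of the stated figure.**

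| Reading | Power for 5 points |
|---|---|
| One-sided, pooled | 77% up, 84% down |
| One-sided, 0.20 × 0.80 as variance in both cities | 80.4% (minimum 4.97 points) |
| Two-sided, same variance | 70.5% (minimum 5.6 points) |

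Of these simple variants, only the second gives the stated figure, and the article does not say that a one-sided test was meant.

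**3. The planned difference in changes.** With baseline variance throughout:

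SE = √[4 × 0.16 × (1 − ρ) × DEFF / (800 × (1 − loss))]; power = Φ(0.05/SE − 1.96); detectable change = 2.80 × SE.

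| ρ | DEFF | Loss | SE (points) | Power | Detectable (points) |
|---|---|---|---|---|---|
| 0 | 1 | 0 | 2.83 | 42% | 7.9 |
| 0.5 | 1 | 0 | 2.00 | 70.5% | 5.6 |
| 0.6 | 1 | 0 | 1.79 | 79.8% | 5.0 |
| 0.7 | 1 | 0 | 1.55 | 90% | 4.3 |
| 0.5 | 1.5 | 15% | 2.66 | 47% | 7.4 |
| 0.6 | 1.5 | 15% | 2.38 | 56% | 6.7 |
| 0.7 | 1.5 | 15% | 2.06 | 68% | 5.8 |

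The stated 80% therefore corresponds to a correlation of about 0.6 with no clustering penalty and nobody lost.

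**4. The thresholds at the assumed baseline.** 10% of 20% is 2 points; 20% of 20% is 4 points. Simple two-sided power with 800 per city:

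- 20% to 22%: 16%. 20% to 18%: 17%.
- 20% to 24%: 49%.

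Repeated measures help only in part. With no clustering or loss, ρ = 0.7 gives Φ(0.02/0.01549 − 1.96) = 25% for 2 points and Φ(0.04/0.01549 − 1.96) = 73% for 4 points. This step needs no outside figure to show the mismatch: both thresholds lie below the five points that the article itself gives as its minimum.

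**The case against.** **The figure might be obtainable.** Sidedness and formula are not stated, and a one-sided calculation with the baseline variance in both cities gives 80.4%. This stands, and it limits the point to the conventional two-sided reading. It does not rescue the claim: no one-sided test is announced, and that calculation also leaves out clustering and loss.

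**The repeated measures might supply the power.** At a correlation of 0.7, power is 90% before clustering and loss, and with a design effect of 1.2 and 10% loss five points remains just detectable: √(0.64 × 0.3 × 1.2 / 720) = 1.79 points, as in the ρ = 0.6 row. So a reader who infers that the design cannot have 80% power goes further than the article allows. What can be said is that the power depends on an unstated correlation.

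**Adjustment might help.** If baseline covariates explained 20% of the variance, the simple two-sided minimum would be 5.60 × √0.8 = 5.01 points. Adjusting for the baseline response at correlation 0.5 would give 79% (up) or 86% (down). But the specified model is the city-by-time interaction, demographic covariates are only optional, and the power statement mentions no adjustment.

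**The design effect and loss are assumed.** True. Stable differences between settlements cancel in within-person change, so a cross-sectional design effect may overstate the penalty. People intending to move within six months are excluded, which should limit loss. The ranges are illustrations. It still stands that the calculation has no margin for either.

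**A tempting stronger reading concerns the baseline.** The article reports that "55% of Hausa girls between the ages of 15 and 19 were married", and one might infer a baseline near 50% for the attitude outcomes. The article does not support this: the figure is a marriage rate in a national sample, not an attitude among adults aged 40 or older in these two cities. A higher baseline also cuts both ways. It lowers power for five points (52% at a 50% baseline), but it enlarges a relative threshold (10% of 50% is 5 points; 10% of 70% is 7 points, power 84%).

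**Conclusion.** The point holds in a limited form. On the conventional two-sided reading the stated 80% is wrong: 67% for an increase and 75% for a decrease. For the planned difference in changes it is right only with a within-person correlation of about 0.6 or more, independent sampling and full follow-up. The first is unstated, and the sampling and follow-up plans do not match the other two. Under an assumed design effect of 1.5 and 15% loss, correlations of 0.5 to 0.7 give 47% to 68% power and a detectable change of 7.4 down to 5.8 points.

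Independently of those assumptions, at the article's own 20% baseline the agreed thresholds of 2 and 4 points fall below its claimed five-point limit. The stated aim of detecting those effects or smaller ones is therefore not met at that baseline. At higher baselines this part eases.

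It would be tempting to name one replacement figure as the study's true sensitivity. The article does not support that either, since correlation, loss and clustering of change are all unknown.

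**What to change.** 1. State sidedness, the formula and the assumed within-person correlation behind the power figure.
2. Replace the single figure with a table of power, or of the detectable difference in changes, for 1600 recruited. Let it run over baseline proportion, correlation (for example 0.3 to 0.7), design effect and retention.
3. When the baseline survey closes, put in the observed baseline proportions and cluster sizes. Keep correlation, loss and clustering of change as labelled assumptions, because one survey round cannot reveal them.
4. Show each relative threshold in percentage points at the assumed or observed baseline. Withdraw or qualify the statements, in the sample size section and under Limitations, that the study is powered for those thresholds and for relatively small effects.

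The cost is a recalculation and revised wording, with no additional participants. The downside is that the published figure becomes less favourable.
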